#### Patient risk assessment

A cognitive assistant is built using AI-based methods for providing representative estimates of melanoma risk to the clinicians, combining different data modalities. The incremental contribution of individual risk factors is combined, including clinical metadata (collected in participant surveys), phenotype characteristics (extracted from total body photography), and genetic risk (calculated PRS and presence of high-risk pathogenic variations). Previous reported weightings for lifestyle and clinical risk factors for melanoma, collected in participant metadata surveys are applied (42, 43). Risk models are then fine-tuned using state-of-the-art data-driven AI-based analysis methods, as non-negative neural networks, to reveal new possible factors that may contribute to risk through the interaction of multiple attributes.

The final individual melanoma risk scores, derived from various data modalities across multiple patient visits, will be combined to generate a global melanoma risk estimation. This holistic assessment offers clinicians the capability to review and thoroughly evaluate the factors contributing to the reported risk score, facilitating a comprehensive understanding of the patient’s melanoma risk.

#### Lesion risk assessment

To assess the risk associated with a lesion, the outputs from previously described models are essential. These algorithms provide information of lesion size, color, diagnosis and skin tone used in the risk assessment algorithm as well as patient risk scores. This lesion risk assessment algorithm furnishes a final risk score ranging from 0 to 1 for each identified lesion. This score is normalized based on the severity of the skin disease characteristics detected, for example between seborrheic keratoses and melanoma. A score of 0 indicates healthy skin, while a score of 1 signifies a high risk of skin cancer. The algorithm will incorporate knowledge of specific skin diseases and conditions to evaluate risk, leveraging well-established characteristics in this assessment.

#### Integration of explainable AI

Explainable AI (XAI) techniques are employed to gain insights into the decision-making processes and rationales of underlying AI algorithms used for diagnostic predictions. While local explainability methods, like layer-wise relevance propagation (44), are utilized to identify the most significant input features (i.e., pixel values) for the diagnostic AI algorithm’s predictions, global XAI approaches, such as spectral relevance analysis (45), reveal global prediction strategies employed by the model.

Furthermore, concept based explainability methods, e.g., concept relevance propagation (46), combine both perspectives, and explain individual prediction with human-understandable concepts employed by the diagnostic AI tool. This further allows the automated generation of XAI-based metadata, e.g., based on the existence of certain concepts, which, for instance, might align with domain expert knowledge. Alternatively, the occurrence of artefact-related concepts (e.g., skin markings), can be used for the automated flagging of data samples.

Moreover, as suggested in the “Reveal to Revise”-framework (47), explainability techniques are seamlessly integrated into the AI model development life cycle. This involves leveraging metadata generated through XAI to iteratively identify and address model irregularities. For instance, the approach involves rectifying issues such as the utilization of data artefacts. This integration enhances the robustness and trustworthiness of the employed AI models over time.

### International skin image analysis challenge

In recent years, it has been a common research practice to organize international competitions or challenges in which the algorithms of different researchers can be benchmarked on publicly released datasets.

Over the period of the iToBoS project, the wider consortium will organize two competitive challenges where world-leading groups can participate in solving new problems on: (1) lesion detection and boundary segmentation in regional (total) body images, and (2) on lesion classification.

These challenges will facilitate advancements in the development of AI and computer aided diagnostic tools and contribute to the knowledge dissemination in the field. A selection of non-identifiable skin images prepared in this study may be included in larger datasets for the analysis challenges. In this instance, minimal clinical non-identifiable information will also be included (age, sex, melanoma history, hair and eye color and body site of image), and whether certain genetic changes, i.e., risk associated genotypes are present.

### Data management and quality assurance

Data management in iToBoS is controlled by a pre-defined Data Management Plan, which describes how we collect, store, organize, maintain, retrieve, and use information in a secure and effective manner. The primary platform of data management is the iToBoS cloud—a private cloud hosted within the Hungarian HUN-REN research cloud, which provides storage, compute and GPU capabilities for the various processing components of the project. All data is ultimately stored and processed in or via the iToBoS cloud. The Storage Cloud is based on Nextcloud software. Access to Nextcloud is managed by internal authentication and authorization backend. New users can be added by the administrators. The operating system of the virtual machines and the data stored in the cloud are encrypted leveraging the LUKS (Linux Unified Key Setup) technology provided by the Compute Cloud service. The Compute Cloud runs on OpenStack. The cloud infrastructure is accessible only by the project members using SAML (Security Assertion Markup Language) authentication. The compute cloud can host the necessary virtual machines for the project. The virtual machines can be run in a private network, which is not accessible from the outside world. It is also possible to create multiple private networks to separate the virtual machines within the project. The cloud compute provides a firewall which by default blocks all incoming traffic to the virtual machines. The virtual machines can be accessed using SSH (Secure Shell) protocol, which is protected by public key. The iToBoS cloud also provides GPUs for AI inferencing tasks.

### Data monitoring

#### Patient consent, metadata, and image acquisition

Site reviewers will randomly select 10 participant visits on a monthly basis to retrospectively check for adherence to protocols in regard to:

Patient consent for completeness and accuracy.Input of data into eCRFs for completeness and accuracy.Images produced by VECTRA in regard to positioning of participants, consistency, and image quality.

Feedback from monitoring visits is to be provided to clinical sites quarterly.

#### Image annotation

The first subset of participant image datasets pre-annotated by the ISAHIT workforce are 100% reviewed by the clinical sites for accuracy, with feedback provided after each dataset is reviewed. This process is repeated until accuracy has reached at least 80% agreement between ISAHIT annotators, and the clinical sites. After which, 10% of datasets pre-annotated by ISAHIT will receive clinician review, with direct feedback provided if annotation is rejected.

For lesion classification annotation performed by expert dermatologist, an initial review stage will take place after each clinical site has annotated 10 participant datasets. Each dataset will be reviewed by a different clinical site to calculate agreement between two expert dermatologists. If agreement is over 95%, then lesion classification annotation will continue without further review. If agreement is under, then the panel of dermatologist annotators will meet to discuss cases in disagreement. Dermatologists will then annotate and provide review for another 10 patient datasets and repeat this process until agreement is over 95%.

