#### Sample size

Optimal sample sizes for AI-based image classification tasks are difficult to estimate. Therefore, for the purpose of this study, a target sample size of 500 patients will be recruited. It is expected that 15% (*n* = 75) will be low/average risk for melanoma, 50% (*n* = 250) will be moderate/high risk, and 35% (*n* = 175) will be very high risk. The majority of the patients will have up to six sequential TBP captures, taken at intervals of every 6 to 12 months. From each TBP capture, an average of 500 image tiles (8 cm × 10 cm) will be produced, annotated and available for development of the photodamage CNN algorithm.

Over a 2 years period, considering the melanoma incidence in Queensland (Australia) (15), we anticipate incidence rates of 0.3, 1.2, and 2.8% for individuals classified under low/average risk, moderate/high risk, and very high risk, respectively. Therefore, we expect 8 annotated melanomas (*n* = 0.2, *n* = 3, *n* = 5 in sequence). Correspondingly, it is expected that there will be 67 keratinocyte cancers for every melanoma diagnosed (16). Therefore, we expect 549 keratinocyte cancers (13 in the low/average risk group, 201 in the moderate/high risk group and 335 in the very-high risk group).

With respect to benign lesions, the median general population total body nevus counts >2 mm in diameter in the Queensland general population are 32 nevi per person (17). Higher counts are expected for those at higher risk of melanoma with a median number of nevi >2 mm in diameter reported in a Swiss cohort at 189 per person (18). We therefore conservatively estimate those at moderate/high risk to have a median around 80 nevi >2 mm in diameter. Hence, a total of approximately 66,475 nevi (2,400, 20,000, 33,075 respectively) will be annotated across 500 individuals at one time point. We estimate a ratio of 1:4 for nevi:other benign lesions (19), and therefore estimate an additional 265,900 other benign lesions for annotation.

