#### Annotation software

V7’s *Darwin* platform facilitates the viewing and complex annotation of the skin image tiles. The platform enables users to designate a workflow in which images are assigned to various HITers and subsequently reviewed by clinical sites. Users across this workflow can view and edit image labels simultaneously, while allowing reviewers to provide comment, explanation and reject incorrectly annotated images.

Each dataset of image tiles represents one VECTRA TBP capture for one patient. Once uploaded to the V7 Darwin platform, any detected lesions are auto-annotated with an ‘*unlabelled*’ tag. Every image tile contains a circular digital ruler with a standardized diameter of 2.5 mm, enabling HITers to measure lesions during the annotation process. The HITers are instructed to review the auto-annotated lesions for falsely pre-tagged lesions, either because they measure <2.5 mm, or because they are artefacts (e.g., umbilicus, hair, scratch/scar etc.). Likewise, annotators will need to adjust segmentation borders when multiple lesions have been grouped together by the auto-annotating software. HITers are then instructed to update the ‘unlabelled’ tag to a lesion color category (Brown, Pink/Red/Purple, Black, Blue, White, Skin Color, or Combination). Lastly, HITers will categorize the average sun damage for each image tile as (1) None/Mild, (2) Moderate, or (3) Severe. Annotators are provided with image examples to use as reference in their assessment. An example of the Darwin user interface is displayed in Figure 2.

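### The 95% agreement rule that ends review of diagnostic labels has no class-specific requirement, so it can be met whatever the agreement on cancers, which are about 0.2% of lesions

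*Protocol article*

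**What the plan says.** The rule is in the protocol article under Data monitoring, Image annotation. For the diagnostic classes of Table 1, "an initial review stage will take place after each clinical site has annotated 10 participant datasets". The comparison is between two readers: "Each dataset will be reviewed by a different clinical site to calculate agreement between two expert dermatologists". The consequence of passing is "If agreement is over 95%, then lesion classification annotation will continue without further review". The panel of annotating dermatologists meets over disputed cases only when agreement falls short, after which another 10 datasets are read and the check is repeated.

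The unit under review is defined under Annotation software: "Each dataset of image tiles represents one VECTRA TBP capture for one patient". A reviewed dataset therefore holds all annotated lesions of a whole capture.

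The expected mix of lesions is under Sample size. For 500 patients, "Therefore, we expect 8 annotated melanomas", 549 keratinocyte cancers, 66,475 nevi and 265,900 other benign lesions.

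The section on the pre-annotation workforce explains why its own accuracy threshold may be lower (80%): errors there matter less than errors in cancer detection. Pre-annotation nevertheless keeps a continuing 10% clinical review. No continuing review is stated for the diagnostic labels.

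**The concern.** The stricter threshold is meant to protect the labels on which cancer detection depends. One overall percentage across 14 classes is dominated by the commonest classes, and on the article's own counts nearly all lesions are benign. The figure can exceed 95% whether the readers agree on all, some or none of the cancers.

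Passing has two effects: review ends, and lesions on which the readers differed, cancers included, go to no panel. The labels then serve to train, tune and test the classifier (Data splitting; Skin lesion classification) and feed the lesion risk score. The test set carries labels from the same process, so testing would not by itself expose a weakness in the malignant classes.

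**Working it through.** **Inputs (Sample size).** "a target sample size of 500 patients will be recruited", split 75 / 250 / 175 by risk group; "we anticipate incidence rates of 0.3, 1.2, and 2.8% for individuals classified under low/average risk, moderate/high risk, and very high risk, respectively"; "it is expected that there will be 67 keratinocyte cancers for every melanoma diagnosed"; 32, 80 and 189 nevi per person in the three groups; four other benign lesions per nevus.

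**Step 1. The article's own counts.**
- Melanomas: 75×0.003 + 250×0.012 + 175×0.028 = 0.225 + 3.0 + 4.9 = 8.125. Stated 8; reproduces.
- Keratinocyte cancers: 67×(0.2 + 3 + 5) = 549.4. Stated 549; reproduces.
- Nevi: 75×32 + 250×80 + 175×189 = 2,400 + 20,000 + 33,075 = 55,475. Stated 66,475; does not reproduce (11,000 too high).
- Other benign: 4×66,475 = 265,900 as stated; 4×55,475 = 221,900 from the re-added total.

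Both totals are carried forward. Cancers are 8 + 549 = 557.

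**Step 2. Cancer share and agreement.** Share = cancers / all lesions. If one reader calls every cancer benign and all else agrees, agreement = 1 − share. If both readers mark the same number of cancers but never the same lesion, agreement = 1 − 2×share.

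| | Stated nevus total | Nevi re-added |
|---|---|---|
| All lesions | 332,932 | 277,932 |
| Cancer share | 0.167% | 0.200% |
| Agreement, one reader misses every cancer | 99.83% | 99.80% |
| Agreement, readers mark different lesions | 99.67% | 99.60% |
| Lesions per 10 datasets (total / 50) | 6,659 | 5,559 |
| 5% allowance per 10 datasets | 333 | 278 |
| Cancers per 10 datasets (557 / 50) | 11.1 | 11.1 |

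The allowance is 25 to 30 times the number of cancers. On the stated counts, kappa for cancer versus not is 0.00 in the first case and −0.002 in the second. Specific agreement, 2a/(2a+b+c), where a lesions are called cancer by both readers and b and c by only one, is 0 in both because a = 0.

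**Step 3. Sensitivity.** With nevi and cancers only, the share is 557/67,032 = 0.83% or 557/56,032 = 0.99%, and agreement is still at least 98.0%. Cancers would reach 5% of lesions only with 557×0.95/0.05 = 10,583 benign lesions, about 21 per person, against about 555 to 665 expected. Cancers are counted over two years and benign lesions at one time point, so the share in a single capture is probably lower still.

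**Step 4. Melanoma in a review round.** Assume 8.125 melanomas spread evenly over 500 patients, with Poisson counts.
- One site's 10 datasets: 8.125/50 = 0.1625 expected; P(at least one) = 1 − exp(−0.1625) = 15%.
- Three annotating sites, 30 datasets: 0.4875 expected; P(at least one) = 1 − exp(−0.4875) = 39%.

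**Step 5. Suspicious melanocytic lesions (SM).** The article gives no count, so the share is an assumption. Let s be the share of lesions called SM, all disputed, together with every cancer (0.2%). Agreement is 100% − s − 0.2%: 98.8% at s = 1%, 96.8% at 3%, 95.0% at 4.8%. The rule is still met if s is below about 4.8%. Here s counts lesions called SM by either reader. If the readers never mark the same lesion, the limit per reader is (5% − 0.4%)/2 = 2.3%.

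**The case against.** **The measure is not defined.** The article speaks only of agreement. It does not call it raw, and does not say that it is taken over all lesions. A condensed article may leave a fuller definition to the full protocol. This stands as a limit on certainty. However, the threshold, the sample and the consequence of passing are all stated, and an unqualified percentage on whole-patient datasets is most naturally read as percent agreement over their lesions.

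**The worst case is extreme.** It assumes complete disagreement on cancers and perfect agreement on more than 5,500 benign lesions per 10 datasets. Real readers will also differ on benign classes, and those differences use up the 5%. That is correct: the 99.6% to 99.8% is a bound, and 95% over 14 classes may be demanding. But it does not make the figure informative about cancers. Moving from full agreement to none on cancers shifts the overall percentage by only 0.17 to 0.40 points.

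**There are safeguards.** Cross-site second reading, panel discussion and repeat rounds are real. The panel and the repeats, however, are triggered only when the overall figure falls short.

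**Stronger readings that a reader might infer.** One is that the malignant labels are, or will be, unreliable; nothing in the article shows this. Another is that a review round has only a 15% chance of containing a melanoma; that figure is for one site, and three sites together give about 39%. A third is that the rule is equally uninformative about SM; with no SM count, and 85% of the cohort at moderate to very high risk, this holds only below the limit in Step 5.

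**Conclusion.** The point holds for MM, BCC and SCC. On the plain reading of the rule, the agreement figure that ends review barely depends on agreement on cancers, which are 0.17% to 0.20% of expected lesions. It would stand at about 99.6% to 99.8% with every cancer disputed and everything else agreed. For SM the same conclusion is conditional on its share of lesions.

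This rests on two assumptions: that agreement means percent agreement over all lesions in the reviewed datasets, and that the lesion mix is as expected under Sample size. The nevus addition error does not alter the conclusion. The result shows what the rule can let through, not what will happen. It should be fixed, because it is the only reliability check stated for the diagnostic labels, but it does not show that the dataset is unsound.

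**What to change.** - Define the agreement statistic. Keep 95% overall as a secondary check.
- On the same double-read datasets, pooled over sites and rounds, compute specific agreement 2a/(2a+b+c) for the suspicious and malignant group. Report it separately for melanocytic classes (SM/MM) and keratinocytic classes (BCC/SCC/AK-IEC), with lesion numbers and a confidence interval.
- Set a threshold for it in advance, and require that it be met before review may stop. The documents give no basis for a particular value, so the sponsor must choose and justify it.
- Send every lesion that either reader placed in this group, and on which they differ, to the existing panel, even when overall agreement exceeds 95%.
- State that melanoma itself will be too rare for its own criterion: fewer than 0.5 are expected in 30 datasets, among about 33 cancers (3×11.1).

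**Cost.** The monitoring rule is reworded, and the readers, datasets and panel stay the same. Agreement on these classes will look lower than 95%, and some extra review rounds and panel cases may be needed. No saving in reading load should be expected, since both readers must label whole datasets before the disputed lesions can be identified.

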### Ethics and dissemination

Clinical data acquisition studies received Human Research Ethics Committee (HREC) approvals from The University of Queensland HREC (2022/HE001866) for the Brisbane, Australia site, and from the Hospital Clinic of Barcelona HREC (HCB/2022/1051) for the Barcelona, Spain site. The study has been registered with ClinicalTrials.gov (ref NCT05955443). The study was conducted in accordance with the principles of Good Clinical Practice. The study was designed following the ethical principles of the Declaration of Helsinki from 1964. Results will be published in peer-reviewed journals and disseminated at international scientific meetings.

### Patient and public involvement

The iToBoS Consortium include partnership with the Melanoma Patient Network Europe (MPNE), to ensure direct consultation and dissemination of research to melanoma patients and the public. MPNE reviewed this protocol prior to implementation to provide feedback on the study design on behalf of the melanoma patient network. Furthermore, MPNE are running a series of workshops for MPNE members over the course of the project, which include presentations and questions time with iToBoS Consortium researchers.

Additionally, iToBoS Consortium partner The University of Queensland hold regular consumer forums, to provide a platform for researchers, advocacy groups and consumer representatives to meet and exchange ideas. These forums also include presentations on recent research developments related to melanoma, with ample time allocated for consumer questions and discussion (48).

## Anticipated results

At the completion of this study, we anticipate having a comprehensive annotated dataset of total body photography images, anonymized, and labelled with patient-level metadata. Images will be annotated with information relating to skin phenotype and lesion diagnostic categories. Patient-level metadata will enable machine learning protocols to evaluate individual risk for melanoma. The AI tools we anticipate will include algorithms for lesion detection, segmentation, matching (from previous imaging), change detection, ugly duckling assessment, and lesion diagnostic category. All these algorithms contribute to the final output of lesion risk assessment. A second holistic patient risk algorithm will be developed using patient-level metadata and skin phenotype information.

Furthermore, with research partners dedicated to the development of explainable AI (XAI) procedures, we anticipate incorporating XAI description with all risk assessment algorithm output. Lastly, it is our objective to contribute annotated datasets to two international computer skin image analysis challenges to advance further developments in this field and promote wider collaboration.

## Discussion

To our knowledge, this protocol is the first to describe the multiclass annotation of total body photography (TBP) for both skin lesion and phenotype characteristics. This includes DICOM labelled patient-level metadata designed for machine learning application. Algorithms developed with these datasets will address several clinically relevant gaps that previous skin lesion classifier algorithms often lack (49). The majority of algorithms to date are trained to consider a dermoscopic image of a lesion, in isolation of any clinical background. This has negatively impacted the translation of this technology into clinical practice. In a real-world scenario, a dermatologist would consider a patient’s medical history, phenotype (including skin/hair/eye color, nevi characteristics, and UV damage), review sequential imaging to detect lesion changes, and apply ‘ugly duckling’ methods, which draws attention to lesions that are unlike others on a given patient. The aim of this protocol is to develop computer aided diagnostic (CAD) tools capable of providing holistic risk assessment of both patient and individual lesions.

One advantage this protocol presents is the prospective collection of TBP from patients at various risk of melanoma, providing a representative image dataset of the entire skin surface for both general and higher risk populations. To date, algorithms for skin lesion classification are often developed using retrospective public datasets of mostly dermoscopy images, which may be restricted to ‘interesting cases’ and lack generalizability to day-to-day clinical practice (6). Furthermore, an algorithm applied to TBP or other wide-field clinical images, increases usability as a triage tool by non-dermatologists. Any AI triage tools dependent on dermoscopy images, must assume that the end-user has professional training to identify lesions requiring specialist review. In the scenario of a telehealth TBP appointment where dermatologists are not involved in the imaging, the imaging technicians could be prompted by AI tools to take additional dermoscopy images of lesions flagged as suspicious or malignant.

A current challenge, particularly given the present melanoma overdiagnosis epidemic, is identifying those who are at the highest risk of melanoma and would benefit the most from screening and surveillance (50). Existing risk stratification methods often rely on subjective assessments or self-report which result in varying levels inter- and intra-rater reliability and can lead to misclassification (51, 52). This protocol uses experts to provide ground truth ratings using reproducible strategies, resulting in high quality data for training machine learning algorithms. Once trained, the algorithms will be able to provide automated and objective measures of phenotypic risk factors, removing the subjectivity of single raters and self-report.

Previously, the use of conventional total body photography imaging combined with sequential digital dermoscopy imaging has been shown to reduce the number of biopsies taken, as well as increasing the accuracy and timeliness of diagnosis in people at high risk of melanoma (53, 54). Therefore, incorporating an objective lesion-based risk as well as personal-based risk with these technologies has the potential to further aid in the early detection of melanoma, and reduce biopsies of benign lesions.

